# Effects of transcranial direct current stimulation on patients with disorders of consciousness after traumatic brain injury: study protocol for a randomized, double-blind controlled trial

**DOI:** 10.1186/s13063-019-3680-1

**Published:** 2019-10-17

**Keywords:** Transcranial direct current stimulation, Disorders of consciousness, Traumatic brain injury, Randomized controlled trial

## Abstract

**Background:**

Disorders of consciousness (DOC) after traumatic brain injury (TBI) raise the mortality of patients, restrict the rehabilitation of patients with TBI, and increase the physical and economic burden that TBI imposes on patients and their families. Thus, treatment to promote early awakening in DOC after TBI is of vital importance. Various treatments have been reported, but there is no advanced evidence base to support them. Transcranial direct current stimulation (tDCS) has shown great potential in promoting neuroelectrochemical effects. This protocol is for a double-blind, randomized, controlled, clinical trial aiming to research the effects and safety of conventional rehabilitation combined with tDCS therapy in patients with DOC after TBI.

**Methods/design:**

Eighty patients with DOC after TBI will be randomized into one of two groups receiving conventional rehabilitation combined with sham tDCS or conventional rehabilitation combined with active tDCS. The intervention period in each of the two groups will last 4 weeks (20 min per day, 6 days per week). Primary outcomes (Glasgow Outcome Scale (GOS)) will be measured at baseline and the end of every week from the first to the fourth week. Secondary outcomes will be measured at baseline and the end of the fourth week. Adverse events and untoward effects will be measured during each treatment.

**Discussion:**

Patients with central nervous system lesions have received tDCS as a painless, non-invasive, easily applied and effective therapy for several decades, and there has been some evidence in recent years showing partial improvement on the level of consciousness of partial patients with DOC. However, reports mainly focus on the patients in a minimally conscious state (MCS), and there is a lack of large-sample clinical trials. This protocol presents an objective design for a randomized controlled trial that aims to study the effectiveness of conventional rehabilitation combined with tDCS therapy for DOC after TBI, to evaluate its safety, and to explore effective and economical therapeutic methods.

**Trial registration:**

Chinese Clinical Trial Registry, ChiCTR1800014808. Registered on 7 February 2018.

**Electronic supplementary material:**

The online version of this article (10.1186/s13063-019-3680-1) contains supplementary material, which is available to authorized users.

## Background

Traumatic brain injury (TBI) is caused by a violent force that affects the head directly or indirectly, and is the leading cause of death and disability among young people around the world [1]. According to epidemiological survey results and expert prediction, by 2020 TBI will become the third largest disease burden in the world. Disorders of consciousness (DOC) refers to the serious impairment of patients’ ability to recognize and perceive the surrounding environment and their own state, which can include coma, vegetative state (VS)/unresponsive wakefulness syndrome (UWS) and a minimally conscious state (MCS) [2]. Many patients with severe TBI will suffer from DOC, and up to 14% of patients with TBI are in a long-term coma or persistent VS after rescue; the longer the duration of coma, the higher the mortality [3, 4]. Therefore, early awakening of patients with TBI can reduce the disability rate and mortality in patients with TBI.

There has been extensive clinical and basic research into treatments for DOC treatments, including electrical nerve stimulation: in DOC this mainly involves median nerve electrical stimulation (MNES) [5–7], spinal cord electrical stimulation (SCS) [8–10], transcranial direct current stimulation (tDCS) [11–13], vagus nerve stimulation (VNS) [14, 15], or deep brain stimulation (DBS) [16, 17]. However, there is no unified DOC treatment guideline [18].

tDCS is a non-invasive brain stimulation technology, which is safe, simple to operate and economical. A previous study [19] has shown that there is no significant untoward effect of tDCS in healthy individuals except for mild tingling (76%), itching (68%), mild burning (54%), and mild pain (25%). tDCS is gradually being applied for treatment of people with motor skills and language impairment after craniocerebral injury, dysphagia, Alzheimer’s disease, Parkinson’s disease, acute and chronic pain, tinnitus, depression and normal subjects, and DOC, as well as in studies such as being tested in healthy individuals [11]. A constant, weak direct current (DC) can effectively pass through the skull and induce bipolar, polarity-related changes through skull conduction on the corresponding cortex. The stimulation effect is determined by the stimulation site, the current intensity, the polarity, and the area of the electrode slice. tDCS works by regulating the activity of spontaneous neuronal networks [12]. At the neuronal level, tDCS regulates excitability in the cerebral cortex. This is mainly due to changes in the polarity of the stimulus, resulting in changes in resting membrane potential depolarization or hyperpolarization, thereby affecting cortical excitability changes in spontaneous neuronal activity. Stimulation usually increases the excitability of the cerebral cortex, and cathodal stimulation reduces the excitability of the cortex [13]. tDCS also increases synaptic plasticity. Besides, some studies have suggested the electrophysiological mechanisms [20–22] and biochemical mechanisms [23, 24] of tDCS, which makes tDCS in DOC more feasible. Nevertheless, clinical research into tDCS combined with conventional rehabilitation in DOC after TBI is rarely reported.

Therefore, the objective of this large-sample, randomized controlled trial is to (1) research the efficacy of conventional rehabilitation combined with tDCS in DOC after TBI; (2) evaluate the safety of tDCS in patients with DOC after TBI; and (3) present the study protocol, the previous results of the clinical trial, ensuring adherence and compliance with the guidelines previously proposed.

## Method/design

### Study design

The clinical study is a prospective, randomized controlled trial designed with double-blinded assessments, and is being carried out in 80 patients hospitalized with DOC after TBI. All participants will be randomly allocated to the intervention group or control group in a 1:1 ratio. The control group will receive conventional rehabilitation combined with sham tDCS therapy, and the intervention group will receive conventional rehabilitation combined with active tDCS therapy. This trial will comprise a 4-week intervention and 8-week follow-up period. The relative primary outcome (Glasgow Outcome Scale (GOS)) will be measured at baseline and the end of every week from the first to the fourth week. The secondary outcomes (Glasgow Coma Scale (GCS), brainstem auditory evoked potential (BAEP), and upper sense evoked potential (USEP) will be measured and electroencephalogram (EEG)) performed at baseline and the end of the fourth week. During each treatment, adverse events, and untoward effects will be measured. The first affiliated Hospital of Nanchang University (NCU), which will undertake the study, is responsible for training rehabilitation therapists on standard operating procedure and supervising the progress of this trial in all clinical sites. In addition, the randomization and blinding will be performed by an independent statistician from the Center of Evidence Based Medicine, NCU. A flow diagram of this trial is presented in Fig. 1

**Fig. 1 Fig1:**
[figure not shown]
Flow diagram of study design. DOC, disorders of consciousness; TBI, traumatic brain injury; tDCS, transcranial direct current stimulation; EEG, electroencephalogram

### Participants and recruitment

The participants will be recruited from the intensive care unit (ICU) and the neurologic intensive care unit (NICU) at the First Affiliated Hospital of Nanchang University. Our study will be advertised on the Internet homepage of First Affiliated Hospital of Nanchang University between December 2019 and December 2020. Posters will select the potential objects who perhaps meet the inclusion criteria by looking through patients’ medical histories via the Computerized Patient Record System (CPRS) and inform patients and their families about this trial is displayed in hospital via phone, or email. Interested families can contact the project leader further. After obtaining informed consent, the prospective participants are screened by a neurologist from the NICU at The First Affiliated Hospital of Nanchang University, according to the inclusion and exclusion criteria. Those who satisfy all criteria are eligible to participate. The eligible individuals are invited to participate in the trial and are directed to a diagnostic assessment by a neurologist, followed by rehabilitation assessments. Consent will be obtained for all study participants from their family members. Data on the design of the study are shown in Table 1.

**Table 1 Tab1:** Data on the design of the study

Point in time	Screening stage	Treatment period 1 (1 week)	Treatment period 2 (2 weeks)	Treatment period 3 (3 weeks)	Treatment period 4 (4 weeks)
Informed consent	X				
Inclusion and exclusion criteria	X				
Withdrawal, drop out and termination criteria		X	X	X	X
Basic information	X				
Past medical history	X				
Therapeutic parameter record		X	X	X	X
Glasgow Coma Scale (GCS)	X	X	X	X	X
Glasgow Outcome Scale (GOS)		X	X	X	X
EEG	X				X
Brainstem auditory evoked potential (BAEP)	X				X
Upper sense evoked potential (USEP)	X				X
Overall efficacy evaluation					X
Complications	X	X	X	X	X
Adverse events recorded	X	X	X	X	X

*EEG* electroencephalogram

### Inclusion and exclusion criteria for the trial

Patients who meet the following criteria will be deemed eligible for the trial: coma: (1) male or female patients aged 18–65 years; (2) severe traumatic brain injury that leads to coma; (3) coma that lasts more than a week; (4) magnetic resonance imaging (MRI) of the head demonstrates no obvious shift, structural damage, extensive necrosis of the brain structure change and obvious brain stem (not including the pyramidal tract) or thalamic lesions with lesions in each lobe not exceeding 30% of the scope of one side of the brain; (5) stable condition and stable vital signs; and (6) the families of the patients volunteered the patient to participate in the study and provided signed informed consent.

VS/UWS and MCS: (1) male or female patients aged 18–65 years; (2) diagnosis as established by the Multi-Society Task Force in 1994 and the current internationally recognized standards for plant status diagnosis; conforming to the current internationally recognized minimum state diagnostic criteria for international studies, such as reported by Giacino in 2002; (3) the course of illness is more than one month; (4) MRI of the head demonstrates no obvious shift, missing, extensive necrosis of the brain structure change and obvious brain stem (not including pyramidal tract) or thalamic lesions, with lesions in each lobe lesions not exceeding 30% of the scope of one side of the brain; (5) stable condition and stable symptoms; (6) the families of the patients volunteered the patient to participate in the study and provided signed informed consent .

Patients who meet the following criteria will be excluded from the trial: (1) the use of sedative sleeping pills, anesthetics, psychotropic drugs, muscle relaxants or Na^+^ and Ca2^+^ channel blockers (such as carbamazepine, etc.) during the evaluation period; (2) ventilator dependence; (3) the course of illness is longer than 1 year; (4) The presence of any materials within the body that would contraindicate MRI, such as pacemakers, dentures, metal prostheses, etc., or open craniocerebral injury or skull defects that would contraindicate electromagnetic stimulation; (5) history of epileptic seizures or epileptic seizures confirmed clinically by EEG; (6) comorbid serious diseases (such as heart, liver, and kidney failure); (7) progressive neurological diseases such as central nervous system tumor or transsexual disease; (8) fever, electrolyte disturbance or unstable vital signs; (9) pregnancy; (10) local skin injury or inflammation; (11) hemostasis, coagulation, and anticoagulation dysfunction, as well as people on anticoagulants; (12) acute massive cerebral infarction; and (13) hyperalgesia in the stimulus area.

### Sample size

The sample size calculation is based on improvement in scores on the Glasgow coma scale (GCS). According to similar published articles [25], the GCS scores after active tDCS and sham tDCS are respectively (12.44 ± 2.51) and (10.43 ± 1.90), *n* = 38. According to a similar study [26], treatment with conventional rehabilitation combined with tDCS can probably improve the GCS by 2.01 points on average in participants receiving this intervention compared to those in the control group. Improvement will be measured according to the same sample size of the estimation formula:
$$ n=2\left[{\left({u}_a+{u}_{\beta}\right)}^2{\sigma}^2\right]/{\delta}^2 $$

With a type I error of 5% (*α* = 0.05) and 90% power (*β* = 0.10), the estimated required sample size is 33 participants per group. Allowing for a 20% dropout rate during the study, a minimum total of 80 participants is needed to reach the target of 40 participants per group.

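### The sample size is labelled as based on improvement in GCS, but its inputs are post-treatment scores, so 33 per group and 90% power are not shown to hold for a comparison of change

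*Protocol article*

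**What the plan says.** The Sample size section of the protocol article names its basis: "The sample size calculation is based on improvement in scores on the Glasgow coma scale (GCS"). It then gives the only means and SDs in the calculation, taken from reference 25: "the GCS scores after active tDCS and sham tDCS are respectively (12.44 ± 2.51) and (10.43 ± 1.90"). The effect is credited to another study, reference 26, which is said to show that the treatment "can probably improve the GCS by 2.01 points on average in participants receiving this intervention compared to those in the control group". The section prints the usual two-sample formula for equal groups, sets alpha at 5% and power at 90%, and concludes that "the estimated required sample size is 33 participants per group". Allocation is 1:1 (Study design).

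The article gives no baseline GCS mean or SD, no SD of change, and no correlation between baseline and follow-up.

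The Statistical analysis section plans a *t* test or a non-parametric test for continuous outcomes. Models are used for adjustment if necessary, with the adjusting variables chosen because they differ significantly at baseline. It does not say whether GCS is compared as a final score or as a change. GCS is recorded at baseline and at week 4 (Table 1, Baseline tests).

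**The concern.** Improvement and final score are different variables with different SDs. In a randomised trial the expected between-group difference is the same for both, so 2.01 can serve either. The SD cannot be carried over in the same way: the SD of a change depends on the baseline SD and on the baseline-to-follow-up correlation. If the groups are compared on improvement, as the section's wording suggests, the stated 90% has no demonstrated basis and could be well off in either direction.

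The attribution matters too. Two citations suggest that the effect and the variability come from separate evidence. If 2.01 is simply the difference between the two means already cited, a single study, for which the text gives n = 38, supplies every input.

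**Working it through.** **Inputs.** Means 12.44 and 10.43, SDs 2.51 and 1.90, delta 2.01, alpha 0.05, power 90%, 33 per group, all from the Sample size section. Sidedness is not stated.

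**1. The plan's figure.** n = 2(u_α + u_β)²σ²/δ², with u_α = 1.960 (two-sided) and u_β = 1.282:

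- σ = 2.51: n = 32.77, rounded up to 33. This matches the plan.
- σ = 2.226, the pooled SD √[(2.51² + 1.90²)/2]: n = 25.77, so 26.
- σ = 1.90: n = 18.78, so 19.
- σ = 2.51, one-sided: n = 26.71, so 27.

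Of these, only the SD after active tDCS with a two-sided test gives 33. Power at 33 per group is 90.2% by the normal approximation and 89.3% by the *t* test.

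**2. Source of delta.** 12.44 − 10.43 = 2.01, which agrees to the second decimal with the figure credited to reference 26.

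**3. Comparison of change.** With follow-up SD 2.51, baseline SD s_b and correlation r,

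SD_change = √(2.51² + s_b² − 2·r·s_b·2.51).

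Both s_b and r are assumptions. Power is for a two-sided *t* test at 33 per group with delta 2.01.

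| r | SD_change, s_b = 2.51 | Power | SD_change, s_b = 1.9 | Power |
|---|---|---|---|---|
| 0 | 3.55 | 62% | 3.15 | 72% |
| 0.2 | 3.17 | 72% | 2.83 | 81% |
| 0.4 | 2.75 | 83% | 2.47 | 90% |
| 0.5 | 2.51 | 89% | 2.27 | 94% |
| 0.7 | 1.94 | 98.5% | 1.80 | 99% |

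SD_change equals 2.51 when r = s_b/(2 × 2.51). That is r = 0.50 for s_b = 2.51, 0.38 for s_b = 1.9 and 0.30 for s_b = 1.5. Below that correlation 33 is too few for change; above it 33 is more than enough.

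For s_b = 2.51, the plan's formula with SD_change gives 53 per group at r = 0.2 (52.4), 40 at r = 0.4 (39.3), 33 at r = 0.5 (32.8) and 20 at r = 0.7 (19.7).

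**4. Week-4 score adjusted for baseline.** The residual SD is 2.51·√(1 − r²), which is never above 2.51 and does not depend on the baseline SD.

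| r | Residual SD | Power at 33 per group |
|---|---|---|
| 0 | 2.51 | 89% |
| 0.2 | 2.46 | 90.5% |
| 0.3 | 2.39 | 92% |
| 0.4 | 2.30 | 94% |
| 0.5 | 2.17 | 96% |
| 0.7 | 1.79 | 99% |

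The one degree of freedom spent on the covariate is negligible.

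**The case against.** A reader might infer that 33 per group and 90% power fail for a comparison of improvement. The article does not support that. Depending on two quantities it does not give, 33 can be too few, about right or ample. Nor is r = 0.5 a universal break-even: it applies only if the baseline SD is also 2.51.

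The sponsor also used the larger of the two SDs, which leaves a margin. With the pooled 2.226 at both times, power for change at 33 per group is about 81% at r = 0.2, 86% at 0.3, 91% at 0.4 and 95% at 0.5. This narrows the possible shortfall but does not remove it at low correlations.

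It is tempting to argue that these are acute patients who change quickly, so that r must be low. The eligibility criteria fit that poorly. They require coma of more than a week, or a vegetative or minimally conscious state of more than a month. They also require a stable condition and allow a course of up to a year.

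The Statistical analysis section names no change-score analysis, and the effect sentence can be read simply as a between-group difference, for which 33 is right. That stands: the power loss is conditional on an analysis the article does not commit to. It does not cure the section's opening statement, which names improvement and supplies no SD for it.

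Finally, GCS is a secondary outcome, and a separate analysis plan could settle its model. But the article already sets an adjustment rule that makes the use of baseline GCS conditional, and the sample size is built on GCS. Whether reference 26 independently reports 2.01 cannot be settled from the article.

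**Conclusion.** The stated basis of the sample size does not match its inputs. The 33 per group is arithmetically correct for a two-sided comparison of post-treatment GCS with delta 2.01 and SD 2.51. For a comparison of change it is unsupported, not shown to be wrong. Over r = 0 to 0.7, power at 33 per group runs from 62% to 98.5% with an assumed baseline SD of 2.51, and from 72% to 99% with 1.9. All these figures take delta 2.01 and follow-up SD 2.51 as given, and assume that the cited post-treatment SD carries over to week 4 of this trial.

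The attribution of 2.01 to reference 26 is doubtful because the figure equals the difference between the two means from reference 25. This is a correction of wording and of one analysis rule, worth making because it removes the dependence on unknown quantities at almost no cost.

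**What to change.** 1. In Sample size, state that the calculation is for GCS score at week 4, with delta = 12.44 − 10.43 = 2.01 from reference 25, sigma = 2.51 (the larger of the two SDs) and a two-sided alpha of 0.05. Remove the description as improvement.
2. Correct the attribution of 2.01 to reference 26, or show where that study reports it.
3. In Statistical analysis, specify that week-4 GCS is compared between groups with baseline GCS as a covariate in every case. This replaces, for GCS, an unadjusted test with adjustment only if necessary or after a significant baseline test.

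The cost is a few reworded sentences and one line on the model. Baseline GCS is already collected, so no patients, visits or data are added.

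### Eighty patients do not cover 20% dropout: 32 per arm remain, one short of the 33 that the plan requires for 90% power

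*Protocol article*

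**What the plan says.** The Sample size section of the protocol article bases the calculation on GCS scores reported after active and sham stimulation, with SDs of 2.51 and 1.90. It expects active treatment to "improve the GCS by 2.01 points on average" relative to control. It prints the usual formula for comparing two means, n = 2(u_a + u_β)²σ²/δ², with a 5% type I error and 90% power, and concludes that "the estimated required sample size is 33 participants per group".

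It then adds the dropout allowance: "Allowing for a 20% dropout rate during the study, a minimum total of 80 participants is needed". The inflation step is not shown, and the section does not say which SD was entered as σ or whether the test is two-sided. Under Study design, patients are "randomly allocated to the intervention group or control group in a 1:1 ratio", so 80 means 40 per arm.

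**The concern.** A dropout rate is a share of the patients enrolled. To finish with a required number, that number is divided by one minus the rate. Multiplying it by one plus the rate always gives too few. The printed 40 per group is what the multiplication gives, and the article calls the resulting total a minimum.

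At stake is whether the required number, the dropout rate, the enrolled total and the power can all be true together. A reader will take 80 patients, 20% dropout and 90% power as one consistent set. If they are not, the trial claims slightly more power than its own inputs support, even for the outcome on which it was sized.

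**Working it through.** **Inputs** (protocol article, Sample size): δ = 2.01 GCS points; SDs 2.51 (active) and 1.90 (sham); α = 0.05; power 0.90; dropout 20%; 40 per arm enrolled. Sidedness and the choice of σ are not stated, so both are inferred from which combination returns the printed 33.

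**Step 1: reproduce the 33.** Two-sided α gives u_a = 1.960, and 90% power gives u_β = 1.282.

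n = 2 × (1.960 + 1.282)² × 2.51² / 2.01² = 2 × 10.507 × 6.300 / 4.040 = 32.77, rounded up to **33**.

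Other readings do not give 33:

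| σ | Sides | n per group |
|---|---|---|
| 2.51 | two | 33 |
| 2.51 | one | 27 |
| 2.226 (root mean square of the two SDs) | two | 26 |
| 1.90 | two | 19 |

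Of the SDs the article quotes, only 2.51 with a two-sided test returns 33.

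**Step 2: reproduce the 40.**

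- 33 × (1 + 0.20) = 39.6, rounded up to **40**, the printed figure.
- 33 / (1 − 0.20) = 41.25, rounded up to **42** per arm, 84 in total. Inflating the total instead gives 66 / 0.8 = 82.5, so 83, or 84 with equal arms.

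Rounding does not explain the gap. From the unrounded requirement, 32.77 / 0.8 = 40.96, so 41 per arm.

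**Step 3: what 40 per arm leaves.**

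- 40 × 0.80 = 32 per arm, below both 33 and 32.77.
- 42 × 0.80 = 33.6 per arm, which is enough.
- Largest dropout that keeps 33 of 40: 1 − 33/40 = 17.5%.

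**Step 4: power** (δ = 2.01, σ = 2.51, two-sided 5%). By the normal formula, power = Φ(δ / (σ√(2/n)) − 1.960). At n = 32 this is Φ(2.01 / (2.51 × 0.25) − 1.960) = Φ(3.203 − 1.960) = Φ(1.243) = 0.893.

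| Evaluable per arm | Normal formula | t test (noncentral t) |
|---|---|---|
| 32 | 89.3% | 88.4% |
| 33 | 90.2% | 89.3% |
| 40 | 94.8% | 94.3% |

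Within either column, going from 33 to 32 costs about one percentage point. The further gap between 88.4% and 90% comes from using the normal formula instead of the t distribution, which by itself would require 34 per arm.

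**The case against.** The strongest objection concerns who counts as lost. The Statistical analysis section plans intention-to-treat and per-protocol analyses and fills missing values by last observation carried forward. GCS is recorded at screening, so a patient who drops out has at least one value to carry forward. All 40 per arm can then stay in the intention-to-treat comparison, with nominal power near 95% on the plan's inputs. It stands that the figure of 32 per arm describes completers and the per-protocol set. It does not reconcile the Sample size section, which itself treats dropouts as lost and sets out to allow for them. The plan also commits to a per-protocol analysis and to comparing it with intention-to-treat. Carried-forward values may, besides, dilute the effect, so the 95% is not assured.

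The second objection is size. The shortfall is one evaluable patient per arm and 0.7 points below 90% by the plan's formula, well inside the uncertainty of the assumed SD and difference. That stands, and it is why restating the figures is a sufficient remedy.

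Third, the loss of power depends on σ = 2.51, the larger of the two SDs. With 2.226, 32 per arm would give about 95%. That is correct, but 2.226 would have led to 26 per group, not 33. The headcount contradiction, 32 against 33, does not depend on σ.

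Finally, GCS is a secondary outcome and the primary outcome is the Glasgow Outcome Scale, so none of this measures power for the primary comparison. That is true, and it is a separate matter.

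**Conclusion.** The concern holds. On the plan's own figures, 80 patients with 20% dropout leave 32 per arm, not the 33 that the plan says it needs, so 80 is not the minimum. Keeping 33 takes 42 per arm, 84 in total: four patients more than planned.

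The consequence is slight: power of 89.3% by the plan's formula, or 88.4% by a t test, for GCS among completers. The power figures assume a two-sided test and σ = 2.51, both inferred because they return the printed 33. The disagreement between the required number, the dropout rate and the total rests on neither assumption.

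**What to change.** Keep 80 patients and correct the sentence in the Sample size section in one of two ways:

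- *80 patients (40 per group) keep 33 evaluable per group, and 90% power, with up to 17.5% dropout*; or
- *80 patients (40 per group) give about 89% power with 20% dropout*.

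Both versions hold under the plan's normal formula. The same sentence should state that σ = 2.51 was used and that the test is two-sided, so that a reader can reproduce 33. If 20% dropout and 90% power are both to be kept as stated, the alternative is to enrol 84 (42 per group).

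Restating costs one sentence and a slightly less favourable figure, with no change to design, conduct or analysis. Enrolling 84 costs four more patients.
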